### Reporting serious adverse events

Serious Adverse Events will be reported in a prospective manner during the period starting from the day of administration of the first dose of study vaccine to each subject and ending with the last study visit or performance of the last study procedure or within one month (minimum 30 days) following administration of the last dose of study vaccine for that subject, whatever is longer. Any serious adverse events occurring during this period, whether or not considered to be related to the study vaccine must be reported by the investigator to the appropriate Clinical Safety Group within 1 calendar day (i.e. 24 hours of initial receipt) within GSK Biologicals and MVI, and to the Local Safety Monitor or within 3 calendar days if this period includes a weekend or public holiday.

The investigator will document all available information regarding the serious adverse event on the Serious Adverse Event pages contained in the individual Case Report Form and fax to the GSK Biologicals and MVI Contacts for Serious Adverse Event Reporting. The investigator should not wait to receive additional information to fully document the event before notifying GSK Biologicals and MVI of a serious adverse event. This initial notification should include, as a minimum, sufficient information to permit identification of:

- the reporter
- the subject
- study vaccine(s)
- adverse event(s)
- date of onset

In the event of a death or a serious adverse event determined by the investigator to be related to vaccination, receipt of the fax must be confirmed by telephone call.

The initial fax report should be followed by a full summary utilising the GSK Biologicals Serious Adverse Event pages in the individual Case Report Form detailing relevant aspects of the adverse events in question. Where applicable, information from relevant hospital case records and autopsy reports should be obtained.

***A post-study AE/SAE is defined as any event that occurs outside of the AE/SAE surveillance period for occurrence of adverse events (defined in Section 8.1). Investigators are not obligated to actively seek AEs or SAEs in former study participants.***

***If the investigator learns of any SAE, including a death, at any time after a subject has been discharged from the study, and he/she considers the event reasonably related to a study vaccine, the investigator will promptly notify the Study Contact for Reporting SAEs.***

~~Instances of death, cancer or congenital abnormality in offspring if brought to the attention of the investigator AT ANY TIME after cessation of the~~~~study should be reported to the Study Contacts for Serious Adverse Event reporting.~~

## Pregnancy

Not applicable.

## Treatment of adverse events

Treatment of any adverse event is at the sole discretion of the investigator and according to current Good Medical Practice. The applied measures should be recorded in the CRF of the vaccinee.

# Subject Completion and Drop-out

## Definition

From an analysis perspective, a 'drop-out' is any subject who did not come back for the concluding visit for the double-blind phase of the study (clinic visit 6 at month 8½, day 256). A subject who returns for this concluding visit is considered to have completed the study.

## Procedures for handling drop-outs

Investigators should make an attempt to contact those subjects who do not return for scheduled visits or follow-up. Information gathered should be described on the Study Conclusion page of the CRF and on Medication/Adverse event forms.

## Reasons for drop-out

It should be specified on the Study Conclusion page of the CRF, which of the following possible reasons were responsible for drop-out of the subject from the study:

- Serious adverse event
- Non-serious adverse event
- Protocol violation (specify)
- Consent withdrawal, not due to an adverse event
- Migrated/moved from the study area
- Lost to follow-up
- Other (specify)

# Data Evaluation: criteria for evaluation of objectives

A reporting and analysis plan (RAP) will be developed by CISM and GSK Biologicals in consultation with MVI and submitted to the DSMB for approval prior to breaking the study blind.

For the purposes of data analysis, there will be two distinct data lockpoints for the study, irrespective of cohort:

- Month 8½ (day 256): at the end of the surveillance period for the primary and secondary objectives, double-blind phase.
- Month 21 (day 630): at the end of the safety and efficacy follow-up, open phase. This data lockpoint will be used for the analysis of tertiary objectives.

## Clinical case definition of malaria

The primary case definition of clinical episodes of symptomatic *P.* *falciparum* malaria used for defining the primary endpoint is shown in Table 4. Other definitions of clinical episodes of symptomatic *P.* *falciparum* malaria of different degrees of malaria severity are also included and will be used as specified in the secondary and tertiary efficacy endpoints for the purposes of evaluating vaccine efficacy.

Table 4: Definitions of symptomatic P. falciparum malaria

| Primary Case Definition for malaria episodes | - the presence of *P.* *falciparum* asexual parasitaemia above 2500 per µl on Giemsa stained thick blood films AND - the presence of fever (axillary temperature  37.5°C) at the time of presentation AND - occurring in a child who is unwell and brought for treatment to a healthcare facility. |
| --- | --- |
| Secondary Case Definition 1 | - the presence of *P.* *falciparum* asexual parasitaemia (**any level of parasitaemia**) on Giemsa stained thick blood films AND - the presence of fever (axillary temperature  37.5°C) at the time of presentation AND - occurring in a child who is unwell and brought for treatment |
| Secondary Case Definition 2 | - the presence of *P.* *falciparum* asexual parasitaemia (any level of parasitaemia) on Giemsa stained thick blood films AND - **history of fever within 24 hours** or documented fever (axillary temperature  37.5°C) at the time of presentation AND - occurring in a child who is unwell and brought for treatment |
| Secondary Case Definition 3 | - the presence of ***P.* *falciparum* asexual parasitaemia above 15 000 per µl** on Giemsa stained thick blood films AND - the presence of fever (axillary temperature  37.5°C) at the time of presentation AND - occurring in a child who is unwell and brought for treatment to a healthcare facility. |
| Anaemia Case Definition | - haematocrit < 25% |

Notes: bold text indicates differences in each definition from the Primary Case Definition for malaria episodes

## Primary endpoint

***Efficacy***

The time to the first clinical episode of symptomatic *P falciparum* malaria (Primary Case Definition for malaria episodes as defined in section 10.1) detected by passive case detection over a 6 month observation period starting 14 days after dose 3 (day 90) in children (1-4 years of age at first vaccination) in Cohort 1 and who have received RTS,S/AS02A malaria vaccine or one of the control vaccine regimes (either hepatitis B vaccine or *Haemophilus influenzae* type b vaccine and 7-valent pneumococcal conjugate vaccine).

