|  | Secondary Case Definition 3 | - The presence of *P.* *falciparum* asexual parasitaemia above 15 000 per µl on Giemsa stained thick blood films AND - The presence of fever (axillary temperature  37.5°C) at the time of presentation AND - Occurring in a child who is unwell and brought for treatment to a healthcare facility. |
|  | Anaemia Case Definition | - Haematocrit < 25% |
|  |  | |
| **Primary endpoint** | The time to the first clinical episode of symptomatic *P falciparum* malaria (Primary Case Definition for malaria episodes as defined above) detected by passive case detection over a 6 month observation period starting 14 days after dose 3 (day 74) in children in Cohort 1 (1-4 years of age at first vaccination) who have received RTS,S/AS02A malaria vaccine or one of the control vaccine regimes (either hepatitis B vaccine or *Haemophilus influenzae* type b vaccine and 7-valent pneumococcal conjugate vaccine). | |
| **Secondary endpoints: Cohort 1** | | |

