# Objectives

## Primary objective

The primary objective of the study is to assess the efficacy of RTS,S/AS02A candidate malaria vaccine against clinical episodes of *P. falciparum* malaria in children aged 1 to 4 years at first vaccination, over a 6 month surveillance period starting 14 days after dose 3 (day 74), in Cohort 1.

See Section 10.2 for delineation of primary endpoint and Section 10.1 for delineation of clinical case definitions.

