**(Amended January 17, 2003)**

Paediatric dose (0.25 ml dose volume) of the RTS,S/AS02A candidate malaria vaccine will be administered at each vaccination. Full doses (0.5 ml dose volume) of hepatitis B vaccine (Engerix-B™), the 7-valent pneumococcal conjugate vaccine (Prevnar®) and *Haemophilus influenzae* type b vaccine (Hiberix™) will be given to the control group.

Subjects who cannot be vaccinated on the originally scheduled date due to an acute illness (on the judgement of the investigator or designate) or scheduling conflicts will be vaccinated within 7 days and undergo all study procedures for this visit on the same day as vaccination. In the particular case of any child found to be febrile (axillary temperature   37.5°C), a blood slide will be taken to investigate malaria parasitaemia. Children will be treated as appropriate for their condition and will be followed up until resolution of any symptoms and be vaccinated if their clinical symptoms resolve within 7 days.

Those who cannot be re-vaccinated within 7 days of their scheduled date will continue all study procedures apart from receiving further study vaccinations.

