### Passive case detection of clinical cases of malaria (all subjects)

If a child presenting to Manhiça District Hospital or Ilha Josina Health Facility reports fever within the preceding 24 hours or has a documented fever (defined as axillary temperature  37.5ºC) the same procedure described above (section 5.2.4) will be followed. In addition, blood will be collected for determination of malaria parasites and haematocrit by the CISM laboratory staff. Duplicate blood slides will be taken and labeled with the same unique laboratory ID number, which will also be recorded on the CISM clinic morbidity surveillance questionnaire. Both slides will be taken to the CISM Laboratory and stained with Giemsa. One will be read immediately (within 2 hours) and the result reported to guide diagnosis and management. The second slide will be kept for a later reading, according to CISM SOPs, and will determine parasite density for data analysis. Both slides will be stored at CISM. In addition, blood samples will be taken and stored for parasite genotyping.

Passive case detection of clinical cases of malaria in both cohorts will start from the day of first vaccination (day 0) and will continue until study end (month 21). For the purposes of analysis, data obtained from passive case detection from day 0 onwards will be used for an intention-to-treat analysis for vaccine efficacy while the surveillance period with respect to the primary, secondary and tertiary endpoints will start from 14 days post dose 3 (day 74).

The clinical case definition for malaria currently used at Manhiça District Hospital and Ilha Josina Health Facility is a history of fever within the previous 24 hours or documented fever (temperature  37.5°C) at the time of presentation plus any level of asexual *Plasmodium falciparum* parasitaemia. This will not be changed for the trial and all cases meeting this case definition will receive treatment for malaria.

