## Concomitant medication/treatment

Any immunosuppressants or other immune-modifying drugs or treatments, any vaccine other than the study vaccine(s) and any antipyretics administered at ANY time during the period starting 30 days prior to the first dose of study vaccine(s) and ending one month (minimum 30 days) after the last dose of study vaccine(s) must be recorded in the CRF with trade name and/or generic name of the medication, medical indication, total daily dose, route of administration, start and end dates of treatment. No follow-up will be done for concomitant medication unless it is related to an SAE or a solicited/unsolicited symptom ongoing at the end of the 30 days after the last vaccine dose.

Any other concomitant medication administered prophylactically in anticipation of reaction to the vaccination must also be recorded in the CRF with trade name and/or generic name of the medication, total daily dose, route of administration, start and end dates of treatment and coded as ‘Prophylactic’. If associated with an adverse experience, the adverse experience code or number should be indicated.

During the efficacy surveillance periods for both cohorts(day 90 to month 21 for Cohort 1 and day 90 to month 9 for Cohort 2), all antimalarial drug usage will be documented to determine the period at risk. All prescribed medication will be captured by the morbidity surveillance system. In addition, non-prescribed medication will be solicited at the monthly field worker visits. All additional usage of antimalarial will be documented on the subject’s CRF.

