### Analysis of efficacy

#### Calculation of time at risk

***First surveillance period*** *(Double-blind phase up to day 256, month 8½)*

For each subject in the ATP and Total cohorts, time at risk begins 14 days after the third vaccination while the time at risk for each subject in the ITT cohort begins on day of first vaccination (day 0).

For evaluation of the primary endpoint, end of the time at risk will be the first clinical malaria episode fitting the primary case definition, or on the last day of the surveillance period (day 256, month 8½) if no episode has occurred prior to this. A similarly approach will be used for the other “time to” analyses, which include the secondary endpoint for time to infection (with respect to Cohort 2) and secondary endpoints examining different case definitions of malaria (with respect to Cohort 1). The end of time at risk is determined in the same way for all cohorts (ATP, Total and ITT).

For the evaluation of efficacy against multiple attacks the time at risk will extend to month 8½ and be applied to all cohorts (ATP, Total and ITT).

Time at risk will be adjusted for absence from the study area and anti malaria drug therapy. The monthly home visits will be used to determine any period of travel outside the study area. Absences from the study area of 2 weeks or more will be recorded in multiples of 1 week. The date of departure will be documented. Similarly if treatment for malaria is administered, the subject will not be considered susceptible to malaria infection for a duration 28 days and this period of time will be deducted from the time at risk.

If a subject is lost to follow-up, withdraws or dies, the observations for that subject will be censored at date of withdrawal or death; or at the midpoint between two monthly home visits if the date of withdrawal or death are not available.

***Subjects will be removed from the risk set when they are not at risk by censoring the records and returned to the risk set at a later time. Commercially available software can fit a Cox model, assuming that, in the analysis data set, each subject is represented by one or more observations, each consisting of a time interval, disease and other covariate values of interest over the time interval.*(Amended January 17, 2003)**

***Second surveillance period*** *(Single-blind phase up to month 21)*

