***Determination of parasite genotyping by polymerase chain reaction***

Each time a malaria smear is obtained ***during the surveillance period for primary and secondary endpoints (day 90 up to and including day 256)***, whether for routine collections or to evaluate clinical symptoms, a few drops of blood will be collected onto filter paper for PCR analysis according to the SOP for this procedure. This collection will be noted on the CRF appropriate to the situation. Samples will be collected, stored individually in plastic bags according to SOP, and transferred to a separate laboratory where PCR analysis will be performed. DNA will be extracted subsequently using standard methods. To determine the effect of RTS,S on parasite subpopulations, the distribution of variable alleles of vaccine and non-vaccine type in the CSP gene will be studied in parasites obtained from subjects vaccinated with the RTS,S vaccine or control vaccine using PCR and specific oligonucleotide or sequencing techniques.

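### Sections 10.2 and 10.3.1 label the start of the efficacy window as day 90, but 14 days after dose 3 is day 74; section 6.9 and Appendix F carry the same wrong start

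*Supplement*

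**What the plan says.** The protocol (as amended January 17, 2003) gives two study days for the same event.

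**Day 74.** The primary objective in section 2.1 runs "over a 6 month surveillance period starting 14 days after dose 3 (day 74), in Cohort 1". The synopsis defines the primary endpoint "over a 6 month observation period starting 14 days after dose 3 (day 74) in children in Cohort 1". Section 5.2.6 states that the "surveillance period with respect to the primary, secondary and tertiary endpoints will start from 14 days post dose 3 (day 74"). Section 5.2.7 uses day 74 for Cohort 2.

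**Day 90.** Section 10.2, the formal definition of the primary endpoint, reads "over a 6 month observation period starting 14 days after dose 3 (day 90) in children". The first bullet of section 10.3.1 (Secondary Case Definition 1) has the same label. Section 6.9 gives the efficacy surveillance periods, during which antimalarial use is documented to determine the period at risk, as "day 90 to month 21 for Cohort 1 and day 90 to month 9 for Cohort 2". Appendix F ties filter-paper collection to the "surveillance period for primary and secondary endpoints (day 90 up to and including day 256").

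**No day number.** Section 10.7.2.1 says: "For each subject in the ATP and Total cohorts, time at risk begins 14 days after the third vaccination". It ends the window on day 256 and deducts 28 days after any malaria treatment.

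Section 10.5 admits to the Total Cohort any child with at least one dose and efficacy data. Under section 5.2.2, children who cannot be vaccinated within 7 days of the scheduled date "will continue all study procedures apart from receiving further study vaccinations".

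**The concern.** Section 10.2 contradicts itself: its words and its day number point to different dates. Episodes in days 74 to 89 are primary events under the words and are ignored under the number. This is the endpoint on which the decision about further development rests, so it should have one start date.

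Two related gaps matter more in practice, because they concern data capture and the analysis set.

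- **Antimalarial use.** If antimalarial use is documented for time at risk only from day 90, the 28-day deduction cannot be fully applied to a clock that starts on day 74.
- **Total Cohort.** A cohort defined by one dose, but with a clock that starts after the third, leaves some of its members without a start date. Leaving them out would condition on an event after randomisation, and a missed dose may be due to fever or acute illness.

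**Working it through.** **Window length.** Dose 3 is on day 60 (sections 5.3 and 5.4, clinic visit 4). The end is day 256 (section 10.7.2.1).

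- 60 + 14 = 74. Section 5.2.9 itself describes day 90 as 30 days after dose 3, and 60 + 30 = 90.
- From day 74: 256 − 74 = 182 days; 182/30.44 = 5.98 months.
- From day 90: 256 − 90 = 166 days; 166/30.44 = 5.45 months.
- The simulation in section 10.6.1 censors at 180 days. From day 90 that would be day 270, after the day 256 lock.
- The multiple-episode endpoint in section 10.3.1 runs from month 2½ to month 8½, which again fits day 74.
- The permitted dose intervals are 27 to 37 days, so dose 3 falls on days 54 to 74, and 14 days later is day 68 to 88. No child vaccinated within these intervals reaches the 14-day mark as late as day 90.

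**The plan's own sample size.** Inputs from section 10.6.1: control attack rate 0.11, vaccine efficacy 50% (so 0.055), lower limit 15%, two-sided 95% interval, 80% power. On the log relative risk scale:

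n = (1.960 + 0.842)² × [0.89/0.11 + 0.945/0.055] / [ln(0.50/0.85)]² = 7.849 × 25.27 / 0.2816 = 704.5

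The plan states 704, and the same formula reproduces all seven rows of Table 5. Expected first episodes: 704 × 0.11 = 77.4 and 704 × 0.055 = 38.7, about 116 in total.

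**If day 90 were followed, with the end fixed at day 256.** The Gompertz parameters are not given, so I assume a constant hazard.

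- Control attack rate: 1 − 0.89^(166/182) = 10.1%.
- First episodes falling in days 74 to 89: 704 × (1 − 0.89^(16/182)) = 7.2 control, and 3.6 vaccine at half the hazard, together about 11.
- The count from day 90 would be about 107 to 109. The net fall is smaller than 11 because children with an episode in those 16 days would count as event-free on day 90.
- Power at 704 per group: standard error = √[(8.917 + 18.834)/704] = 0.1985; 0.5306/0.1985 − 1.960 = 0.713; power 76.2%. Spreading the 11% over 180 days instead of 182 gives 76.7%.
- If the 16 days held 5% to 15% of episodes (assumed range), about 6 to 17 would be affected and power would be about 78% to 73%.

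**Antimalarial records.** A treatment given on or after day 74 − 28 = day 46 can overlap a clock that starts on day 74. The section 6.9 rule covering the period up to 30 days after the last dose names immunosuppressants and other immune-modifying treatments, vaccines and antipyretics, not antimalarials. Non-prescribed use is solicited at the monthly home visits, which begin on day 120 (section 5.2.8). Days 46 to 89 are therefore not clearly covered for non-prescribed use.

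**Total Cohort.** Put side by side, section 10.5 (one dose suffices), section 5.2.2 (children who miss a dose stay under follow-up) and section 10.7.2.1 (clock starts after dose 3) leave these children in the cohort with no defined time at risk.

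**The case against.** The best reply is that the rule can be recovered. The words about 14 days after dose 3 are the same in every statement of the primary endpoint. Section 10.7.2.1 sets each child's clock from the actual third vaccination, and only day 74 fits the other dates. That stands. It means that the drop in power belongs to a reading that the analysis section does not support. It does not excuse leaving the wrong number in the endpoint definition. Nor is the number an isolated slip, because section 6.9 and Appendix F use it as well.

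Several stronger readings are tempting, but the documents do not support them:

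- **The start could be chosen after unblinding.** Sections 6.5.1 and 10 require a reporting and analysis plan to go to the DSMB before the blind is broken. That plan is not shown and may settle the date.
- **Early infections would have no genotype.** Cohort 2 samples are scheduled on days 60 and 74 (sections 5.6 and 5.8.3), and section 5.2.6 stores genotyping blood from passive detection, which runs from day 0. Appendix F conflicts with these in wording; it does not show that samples are missing. The genotype analysis is also exploratory.
- **Antimalarial treatment before day 90 goes unrecorded.** Treatment prescribed at the health facilities is captured by morbidity surveillance (sections 5.2.5 and 6.9), and parents are asked not to medicate at home. The gap is mainly non-prescribed use. The documents give no frequency for it.
- **The Total Cohort result is biased by a known amount.** The documents give no dose 3 completion by arm. The ITT analysis from day 0 keeps all children with at least one dose and efficacy data, although section 10.7.2.2.9 lists it as exploratory.
- **Early efficacy makes the 16 days decisive.** The adult trial cited in section 1.1.1 (71% in the first 9 weeks, 34% over 15 weeks) measured infection in men. It does not size a 16-day shift for clinical malaria in children.

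**Conclusion.** The day 90 label in section 10.2 and the first bullet of section 10.3.1 is wrong, and the intended start is day 74. A reader might infer that the trial is undersized; it is not. The 704 per group reproduces and is consistent with the day 74 window.

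The disputed stretch is 16 of 182 days (8.8%). Only if the label were followed would about 11 of 116 expected first episodes fall outside the window and power drop from 80% to about 76%. Both figures assume a constant hazard.

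Two consequences go beyond wording. Section 6.9 as written does not secure the records needed to apply the 28-day deduction from day 74, mainly for non-prescribed antimalarials. Section 10.7.2.1 leaves Total Cohort children without dose 3 with no start of time at risk. Neither can be sized from the documents. The correction is specific and cheap, and it concerns the primary endpoint, so it should be made.

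**What to change.** - **Sections 10.2 and 10.3.1 (first bullet):** replace day 90 with day 74.
- **Section 6.9:** document all antimalarial use, including non-prescribed use, from at least 28 days before day 74 (day 46), or from day 0 so that the ITT analysis is served too.
- **Appendix F:** align the collection period with the day 60 and day 74 samples and the passive-detection samples already scheduled.
- **Section 10.7.2.1:** give Total Cohort children without dose 3 a start that does not depend on receiving it, for example study day 74 counted from dose 1. Alternatively, state that this analysis is restricted to three-dose recipients and rely on the ITT analysis from day 0 for all vaccinated children.

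The cost is amendment wording plus a few more weeks of medication recording. The day 60 and day 90 clinic visits, where medication is already recorded, can carry it. No change to the sample size is needed.
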